### Randomization and Allocation

#### Overview

The randomization will be performed by a researcher not directly involved in this study using a computer-generated program. Participants will be randomly assigned to either the experimental group (the ICanWALK group) or the control group (the breathing exercise group) in a 1:1 ratio. Allocation will be performed by the same researcher using opaque envelope assignments.

#### Experimental Group

The ICanWALK app was recently developed as an educational tool designed to train skills related to fitting and using a walking aid. The experimental group will use the ICanWALK app on an iPad (Apple Inc), available on the MOVE Improve mobile app for both Android and iOS. The MOVE Improve platform is a valid app designed to teach physical movement and improve sports performance [47-49]. The MOVE Improve is a video-based feedback and interactive tool aiming to serve as a large-scale educational tool. The ICanWALK modules [39] follow the MOVE Improve instructional format. Users select a specific skill and then watch an instructional video on that skill with the key skill components highlighted. The user is then videotaped while performing the skill, and that video is shown beside the instructional video. Next, the user is guided through a series of skill performance questions to evaluate their video. At the end of the module, the user receives a summary assessment score from their self-evaluation. The ICanWALK program currently contains 43 modules that teach walking aid-related skills, including fitting, gait patterns, and navigating stairs [39]. Health science students or research assistants will receive 4 hours of training on navigating MOVE Improve, guiding participants in selecting ICanWALK modules, and recording videos. With assistance from a trained health professional student, participants will complete 2 separate 15- to 20-minute sessions within a 1-week period. Using the ICanWALK program, the participant will learn skills for fitting and using a walking aid. Participants will watch an instructional video on each skill, with the key components of appropriate skill execution highlighted (Figure 2). The participant will then perform the task with their walking aid, and the student/research assistant will record the video. The participant will review the video in the app and compare it to the demonstration video to determine whether each component of the skill was performed correctly. A score will be generated at the end. Participants must master the use of the app to be able to independently repeat the tasks of fitting and using their walking aid.

**Figure 2 figure2:**
[figure not shown]
Screenshot of the main steps in using the ICanWALK (Improving Canadians’ Walking Aid Skills, Learning, and Knowledge) app modules.

#### Control Group

The control group will be attention matched to mimic the time, location, and contact with a trainer of the experimental group [50]. Participants will follow the same schedule as the experimental group but will also complete a breathing exercise module available on the MOVE Improve app. The modules are identical in layout, instruction, and self-assessment of videos to the ICanWALK app but differ in content, as no information related to walking aids and mobility is included in this program (Figure 3). With assistance from a trained health professional student or a research assistant, participants in the control group will complete 2 separate 15- to 20-minute sessions within 1 week. Participants will select the breathing exercise module and then choose the specific skill they wish to practice (eg, breathing exercise for reduced stress and breathing exercise for increased lung function), watch the instructional video, and review the performance criteria. A video of the participant performing the selected skill is then recorded and uploaded alongside the model video to allow for side-by-side comparison. The participant will review the video in the app and compare it to the demonstration video to determine whether each component of the skill was performed correctly. A score will be generated at the end.

**Figure 3 figure3:**
[figure not shown]
Screenshot of the main steps in using the breathing exercises module.

### Study Procedure and Data Collection

The study procedures (timeline and measurement tools) are illustrated in the SPIRIT checklist (Table 1). Participants will be assessed at 3 time points: baseline (T1), after intervention (T2), and 4-week follow-up (T3). After signing the consent form, a study coordinator will schedule the first evaluation session (T1). Preintervention questionnaires will include sociodemographic data (eg, age, sex, gender, walking aid type, reasons for using the walking aid, the duration of walking aid use, and previous walking aid experience), the ABC questionnaire, and self-reported knowledge and confidence in fitting and using the walking aid using a tablet or laptop. Participants will then complete the Walking Aids Skills Test (WAST) and mobility tests (6-Minute Walk Test, 6MWT and Timed Up and Go, TUG test).

**Table 1 table1:** SPIRIT (Standard Protocol Items Recommendations for Intervention Trials) checklist.

Schedule of activities		Enrollment	Assessment	Allocation	After allocation				Closeout
		Screening	Baseline (T1)		Intervention	After intervention (T2)	4-wk follow-up (T3)		
**Enrollment**									
	Eligibility screen	✓							
	Informed consent	✓							
	Allocation			✓					
**Intervention**									
	ICanWALK^a^ app (experimental intervention)				✓				
	Breathing exercises app (control intervention)				✓				
**Assessments**									
	Activities-specific Balance Confidence scale		✓			✓	✓		
	Self-reported walking aid knowledge and confidence		✓			✓	✓		
	Timed Up and Go test		✓			✓	✓		
	6-Minute Walk Test		✓			✓	✓		
	Walking Aid Skills Test		✓			✓	✓		

^a^ICanWALK: Improving Canadians’ Walking Aid Skills, Learning, and Knowledge.

All data will be collected by an assessor who will be blinded to group allocation. The T1, postintervention (T2), and follow-up (T3) questionnaires will be imported into the LimeSurvey platform to allow for completion during the evaluation while ensuring secure data management. The collected data will be anonymized with a code assigned to each participant and will be stored on the institutional platform. Access to data will be limited to authorized personnel.

### Outcomes

#### Primary Outcome

Given the ICanWALK app’s theoretical grounding in self-efficacy, behavior change, and skill acquisition, balance confidence—assessed with the ABC scale—was selected as the primary outcome due to its direct relevance to the intervention’s mechanisms of action [32,43]. The ABC scale offers a validated, context-specific measure of individuals’ perceived confidence in performing daily mobility tasks with a walking aid, capturing both psychological and functional dimensions of change [43]. As such, it serves as a sensitive and theoretically congruent indicator of the intervention’s anticipated impact. The ABC scale is a 15-item self-assessment measure that asks individuals to rate their confidence in balance while performing a series of activities on a scale ranging from 0 (no confidence) to 45 (total confidence) [43]. The raw scores are converted into percentages by dividing the sum of the individual scores by the total score and then scores ranging from 0 (no confidence) to 100% (total confidence). The ABC scale is reliable in individuals using mobility devices [51], healthy older adult community dwellers [52], individuals who have undergone lower limb amputation [51,53], individuals with Parkinson disease [54] or knee osteoarthritis [55], stroke survivors [56], and those with traumatic brain injury [57]. The ABC scale is highly sensitive to fall risk [58]. Previous studies have demonstrated high test-retest reliability (intraclass correlation [ICC]=0.85) and excellent construct validity (*r*=0.60-0.75) with the Berg Balance Scale, Community Balance and Mobility Scale, and TUG test [52,55,56]. The administration time is 10 to 15 minutes.

#### Secondary Outcomes

##### Mobility

Mobility tests will include the 6MWT and the TUG test. The 6MWT assesses walking endurance by objectively measuring the distance covered by an individual during 6 minutes of walking [59,60]. It is a common, valid, and reliable measure of submaximal aerobic capacity in individuals with various conditions that takes about 10 minutes to administer [61]. The TUG test assesses functional mobility and fall risk by recording the time (in seconds) it takes for a participant to stand up, walk 3 m, and sit back down on a chair [62]. Measurement properties of the TUG test have been reported for older adults (test-retest reliability; ICC=0.75) and in patients with hip osteoarthritis (interrater reliability; ICC=0.87) [63,64]. The TUG test takes 1 to 2 minutes to administer.

##### Knowledge and Confidence in Fitting and Using Walking Aids

Subjective self-reported knowledge and confidence in walking aid fitting and using will be documented at T1, T2, and T3 using a 4-level Likert scale ranging from “not at all informed or not at all confident,” meaning any knowledge and confidence, to “well informed or very confident,” meaning high knowledge or good confidence.

##### Walking Aid Skills

The WAST test will be used to objectively assess skills of using walking aid when performing daily life activities (eg, walking on flat solid ground, walking on foam surfaces, and going up or down steep or gentle slope or stairs). The WAST is a 15-item objective assessment that measures an individual’s ability to use their walking aids in various contexts, such as picking up an object from the ground and walking on various grounds such as gravel or slopes. Using a standardized rating system (videos), the evaluator assigns a score from 0 (the participant does not meet most evaluation criteria, is unsafe, or is unwilling to perform) to 3 (the participant performs the skill very competently or advanced). The total score expressed as a percentage (indicating the individual’s performance) is the quotient of the total sum of individual scores over the number of skills performed, ranging from 0% to 100%. The higher the score, the better the performance. Although the psychometric properties of this test have not yet been investigated and published, it has been developed with inspiration from the wheelchair skills program [65,66] but has not yet been validated.

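### The WAST percentage formula cannot give 0% to 100% as written, and its denominator conflicts with the rule that scores a refused skill 0, so attempting more skills could lower the score

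*Protocol article*

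**What the plan says.** All of the scoring text is in the Walking Aid Skills section of the protocol article.

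- Length of the test: "The WAST is a 15-item objective assessment".
- Item scale: for each item the rater "assigns a score from 0 (the participant does not meet most evaluation criteria, is unsafe, or is unwilling to perform) to 3", where the top mark stands for very competent or advanced execution. Refusal is therefore a scored result, with value 0.
- Total: expressed as a percentage, it "is the quotient of the total sum of individual scores over the number of skills performed, ranging from 0% to 100" percent.
- Direction: "The higher the score, the better the performance".

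The WAST is taken at every visit. Study Procedure and Data Collection states: "Participants will be assessed at 3 time points: baseline (T1), after intervention (T2), and 4-week follow-up (T3"). The Statistical Analysis section compares the groups after the intervention by analysis of covariance, with each measure's own T1 score as the covariate. The Introduction lists walking aid skills among the secondary outcomes.

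**The concern.** There are two separate faults in one sentence.

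The first is scale. A sum of 0-to-3 items divided by a count of items is a mean item score. It is not a percentage of the maximum, and the sentence contains no step that turns it into one. For the ABC scale, by contrast, the Primary Outcome section does describe dividing by a total score.

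The second is the denominator. The item rule treats refusal as a 0, which suggests that the item counts. The total rule divides by skills performed, which on its plain meaning leaves out a skill that was refused. The article does not say which rule prevails.

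The second fault matters more, because the number of skills attempted may itself respond to treatment. The ICanWALK modules teach stairs, among other skills, and the WAST tests stairs and slopes. The control modules contain nothing on walking aids or mobility. If the app makes people willing to try skills that they refused at T1, a denominator that grows with each attempt can turn that gain into a loss. Adjusting for the T1 score does not repair this, because the T1 and T2 scores may then rest on different sets of items.

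**Working it through.** **Inputs from the Walking Aid Skills section:** 15 items; item scores 0 to 3; refusal scored 0; total = sum divided by skills performed; stated range 0% to 100%.

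**Step 1: the stated range.** With *k* skills performed and all scored 3, the formula gives 3*k*/*k* = 3 for any *k*. For the full test this is 45/15 = 3. Multiplied by 100, it is 300%. A mean item score of only 1 gives 15/15 = 1, which would already read as 100%. The stated upper limit is not reproduced. It is obtained only by adding a factor of 3 to the denominator:

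- performed-only: 100 x sum/(3 x skills performed)
- fixed: 100 x sum/(3 x 15) = 100 x sum/45

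**Step 2: the effect of the denominator.** Suppose a participant performs *k* skills at T1 with mean *m* and refuses the other *j* = 15 − *k*. At T2 the same *k* skills are unchanged and the *j* others are attempted with mean *b*. In percentage points the change is:

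- performed-only: (100/3) x *j*(*b* − *m*)/(*k* + *j*)
- fixed: (100/3) x *jb*/15

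The performed-only score falls whenever *b* is below *m*. The fixed score cannot fall.

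**Step 3: illustrations.** The item scores are assumed, since the article gives no refusal counts or item data. In each case *k* = 10 and *j* = 5.

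| Old skills (*m*) | New skills (*b*) | Performed-only, T1 to T2 | Fixed, T1 to T2 |
|---|---|---|---|
| 3 | 1 | 30/30 = 100% to 35/45 = 77.8% | 30/45 = 66.7% to 35/45 = 77.8% |
| 2 | 1 | 20/30 = 66.7% to 25/45 = 55.6% | 20/45 = 44.4% to 25/45 = 55.6% |
| 3 | 2 | 30/30 = 100% to 40/45 = 88.9% | 30/45 = 66.7% to 40/45 = 88.9% |
| 2 | 2 | 20/30 = 66.7% to 30/45 = 66.7% | 20/45 = 44.4% to 30/45 = 66.7% |

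In the first row the same performance is a loss of 22.2 points or a gain of 11.1 points, depending only on the denominator. In the second row it is a loss of 11.1 or a gain of 11.1. In the last row the performed-only score does not register the five new skills at all.

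**Step 4: what each fault does to the analysis.** Leaving out the factor of 3 multiplies every score, in both arms and at every visit, by the same constant, so analysis of covariance gives the same *p* value. The denominator is different. It can vary between participants and visits, and between arms if training changes how many skills are attempted.

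**The case against.** The sentence itself calls the total a percentage with limits of 0 and 100, so rescaling to the maximum was evidently intended. This stands: the missing factor is probably a drafting slip, and it has no effect on the test.

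A rule that scores refusals 0 makes sense only if the refused item enters the total. On that reading every item counts, the denominator does not shrink, and trying more skills can only raise the score or leave it unchanged. This also stands as a possible reading, but the word used for the denominator points the other way and nothing else in the article settles the matter.

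A reader might go further and infer that the WAST comparison is biased against the experimental arm. The document does not support that. Bias would need all of the following: refusals left out of the denominator, a material number of refusals at T1, more newly attempted skills in the experimental arm than in the control arm, and lower scores on those skills than the participant's earlier mean. The last condition is plausible, since refused skills are likely to be the harder ones, but none of these figures is given. Where new skills score above the earlier mean, the performed-only score rises. The first row of the table is also close to a worst case, and it describes one assumed participant, not a group effect.

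A reader might likewise infer that the 26 participants who have completed all visits were scored wrongly. The article says only that they were assessed, not how their totals were computed.

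Finally, the WAST is a secondary outcome, openly described as not yet validated, in a trial that calls itself exploratory. That limits the weight of the point but does not remove it.

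**Conclusion.** The point holds in a conditional form. Two things are certain from the text: the formula as written runs from 0 to 3 and not from 0% to 100%, and its denominator conflicts with the item rule on refusal. A wrong sign of change is possible but not certain. It arises only if refused skills are excluded from the denominator and newly attempted skills score below the participant's earlier mean. In the assumed examples, the two denominators differ by 22 to 33 points in the T1-to-T2 change for one participant (22.2 + 11.1 = 33.3 in the first row; 11.1 + 11.1 = 22.2 in the second). If training increases attempts at harder skills, any resulting bias would most likely run against the experimental arm.

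This should be fixed, but it does not threaten the trial's main conclusion. The ABC primary outcome and the sample size are untouched. The reason to settle it now is that the same data could otherwise give two WAST totals that move in opposite directions, with the choice between them left open.

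**What to change.** Replace the scoring sentence with an explicit rule:

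- WAST% = 100 x (sum of item scores)/(3 x 15).
- Items that are refused or performed unsafely score 0 and stay in the denominator.
- If an item cannot be tested for logistical reasons, it is dropped from that participant's numerator and denominator at T1, T2 and T3 alike, so that the denominator becomes 3 x the number of remaining items at all three visits.

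Confirm that participants already assessed are scored by this rule from their item-level data, before any comparison between groups. The cost is a sentence or two in the protocol and analysis plan and a short scoring script. No new data are needed if item scores have been stored. If only totals were kept, check whether the items can be recovered.

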### Data Monitoring

The intervention used in this study is an educational, nonpharmacological approach that adheres to the ethical principles of beneficence and nonmaleficence. Given its low-risk nature, it is unlikely to cause adverse effects. Therefore, the establishment of a data monitoring safety board may not be necessary. However, any adverse effects will be monitored informally by the project coordinators.

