Notwithstanding the numerous benefits of walking aids, inappropriate fit and unsafe use can lead to discomfort, pain, injuries, and even an increased risk of falls. A recent review identified an increased risk of injury when crutches were poorly fitted and used improperly due to a lack of training before use [17]. Inadequate use of walking aids was also found to be associated with a greater risk of falls [15,18]. In US emergency departments, 47,312 fall-related injuries among older adults, which were associated with walking aids (87.3% with walkers, 12.3% with canes, and 0.4% with both), were treated annually between 2001 and 2006 [19]. Furthermore, high rates of walking aid disuse or dissatisfaction were associated with difficult or risky use due to a lack of training before prescription [20]. Although injuries and fall risks could likely be reduced through better education and training, no standardized training program has been documented. A recent study by Best et al [21] that documented the quality of existing online educational resources for mobility device training showed that most walking aid training was in the form of infographics and basic instructions and was not evidence based. Most people obtain walking aids independently from the pharmacies or clinics without receiving instruction or demonstration [20,22]. A standardized and effective approach to training walking aid skills may enhance balance confidence and mobility while reducing the risk of injuries and falls for walking aid users and may be useful for health care professionals (as they are the primary source of care for patients).

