## Discussion

### Anticipated Findings

Through this single-blind, 2-site RCT, we aim to evaluate the primary hypothesis that an education and training tool for the correct use of walking aids will effectively improve balance confidence and secondarily may influence mobility and walking aid skills. This study protocol should allow us to determine whether the novel video-based feedback educational tool, designed to teach and train fitting and safe use of walking aid, is effective in improving balance confidence, mobility, walking skills, and knowledge. This is an exploratory RCT, given the paucity of literature on the effectiveness of mobile educational apps on short- and long-term walking aid use.

To meet the challenges of the lack of formal training programs for users on the fitting and use of walking aids and the lack of standardized information for health care professionals, mHealth apps may constitute an affordable and scalable digital health intervention to address these growing gaps. The findings from this study will provide valuable insights into the effectiveness of this novel app in improving knowledge of walking aid fitting and safe use as well as improving balance confidence and mobility. Recent evidence suggests that physiotherapy interventions delivered through a smartphone or tablet app were effective in improving mobility outcomes in people with a wide range of health conditions (such as neurological disorders [67,68]). The video-based feedback learning method used by the ICanWALK modules is known for rapidly improving memory recall [69], behavior change [70], and motor skill acquisition [71] and, consequently, should prevent falls while improving functional independence.

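### Adverse effects are to be monitored informally, so falls and injuries, especially those at home before T2 and T3, could not be compared reliably by arm

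*Protocol article*

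**What the plan says.** The Data Monitoring section describes the intervention as educational and reasons as follows: "Given its low-risk nature, it is unlikely to cause adverse effects". From this it concludes that a monitoring board may not be needed, and then sets the collection rule: "any adverse effects will be monitored informally by the project coordinators".

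Other parts of the protocol article bear on that rule:

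- **Exposure in both arms.** The Walking Aid Skills section says the WAST covers tasks such as "walking on flat solid ground, walking on foam surfaces, and going up or down steep or gentle slope or stairs". Its lowest score is given, among other reasons, when the participant "is unsafe, or is unwilling to perform". Table 1 schedules it at T1, T2 and T3.
- **Exposure in one arm.** The Experimental Group section describes "43 modules that teach walking aid-related skills, including fitting, gait patterns, and navigating stairs", which participants carry out with their own aid while being filmed. The Control Group section has breathing exercises without mobility content.
- **Hazard named by the authors.** The Introduction says: "Inadequate use of walking aids was also found to be associated with a greater risk of falls".
- **Expectation stated by the authors.** The Anticipated Findings section says that the learning method "consequently, should prevent falls while improving functional independence".

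Table 1 lists five assessments, and none asks about falls, injuries or other events. The Statistical Analysis section promises dropout rates and reasons but no tabulation of harms.

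**The concern.** An article may leave forms and definitions to a fuller document. Here, however, the article states the method, and the method is informal. The rule sets no common question, time window or record for both arms and both sites.

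Three features make uneven capture likely:

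- In the sessions, one arm is watched doing walking tasks and the other doing breathing exercises, so the chance of an event being seen differs by arm.
- Collection falls to the project coordinators. The recruitment section names one study coordinator per site. Only the assessor is stated to be blinded.
- Between the last session and T3, roughly four weeks, participants are at home. Nothing in the schedule provides for asking what happened there.

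At stake is what the final report can say about safety. A low count could reflect few events or few questions, and a difference between arms could reflect different detection. The low-risk premise of the Data Monitoring section could then be neither supported nor questioned from the trial's own data.

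**Working it through.** The documents give no harm rate, harm sample size or harm power, so there is no plan figure to reproduce. The check has two parts.

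**1. Does anything offset the informal rule?**

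| Place in the protocol article | Fall, injury or event item? |
|---|---|
| Table 1, assessments at T1, T2, T3 | None among the five listed |
| Primary and secondary outcomes | None |
| Statistical Analysis | Dropout rates and reasons only |
| Experimental Group, staff training | App navigation, module selection and video recording; event recording not mentioned |
| Data Monitoring | Informal, by the coordinators |

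Nothing offsets it.

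**2. What could a standard record deliver from now on?**

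Inputs: 52 planned (Sample Size); 1:1 allocation (Randomization and Allocation); 26 already through T1 to T3 by November 2025 (Results); 15% dropout (Sample Size).

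Remaining participants: 52 − 26 = 26. If those completed were evenly split (an assumption; the article does not give the split), 13 remain per arm.

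With zero events in n participants, the exact one-sided 95% upper limit for the true risk is 1 − 0.05^(1/n). The upper end of the two-sided exact interval is 1 − 0.025^(1/n).

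| n in the arm | Situation | One-sided limit | Two-sided upper end |
|---|---|---|---|
| 26 | All participants, only if recorded from the start | 10.9% | 13.2% |
| 16 | Uneven split, favourable | 17.1% | 20.6% |
| 13 | Even split | 20.6% | 24.7% |
| 11 | 13 × 0.85 = 11.05, after dropout | 23.8% | 28.5% |
| 10 | Uneven split, unfavourable | 25.9% | 30.8% |

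The rows for 16 and 10 are illustrative. Enrolment since November 2025 would reduce n further.

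**Between-arm test.** With 13 per arm, Fisher's exact test (two-sided) gives p = 2 × C(13,5)/C(26,5) = 2 × 1287/65780 = 0.039 for 5 against 0. For 4 against 0 it gives 2 × 715/14950 = 0.096. The smallest significant split against zero is therefore 5 of 13.

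Even with all 26 per arm, 5 against 0 gives p = 0.051 and 6 against 0 gives p = 0.023. Power at 26 per arm, under assumed participant-level risks, is 1.5% for 5% v 10%, 22% for 5% v 20%, 32% for 10% v 30% and 62% for 10% v 40%.

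These figures measure the limit set by sample size. They do not measure the bias from informal collection, for which the documents give no data.

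**The case against.** The strongest case on the other side has several parts.

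- **Informal does not mean unrecorded.** A student or research assistant is present at sessions and an evaluator scores the WAST, so a fall there would be witnessed. Dropout reasons are documented, although participants may withdraw without giving one. This stands in part: the larger gap is events at home, and the right conclusion is that arms cannot be compared reliably, not that nothing could be tabulated.
- **The exposure is mostly shared.** Foam and slopes are named only for the WAST, which both arms perform and whose items may be declined. Stairs are one example among 43 modules, and no text says every experimental participant trains on them. This stands. What differs by arm is supervised practice of walking-aid skills in general.
- **Falls are not an objective or outcome.** The fall-prevention remark is Discussion commentary on the learning method. This stands, and the trial should not be faulted for failing to test it.
- **The article is condensed.** Two ethics boards approved the protocol, and the SPIRIT checklist is in an appendix not shown. That excuses absent forms and definitions. It does not excuse a method stated as informal.

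A reader might also infer that greater balance confidence leads to more risk-taking before T3, or that the lack of a monitoring board is a defect. The documents contain nothing on the first. The second does not follow for a short educational intervention, and a board would not correct unsystematic collection.

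**Conclusion.** The point holds in limited form. The plan prescribes unstandardised collection of adverse effects and contains nothing to compensate, so falls, injuries and other events, especially those at home before T2 and T3, could not be compared reliably by arm. The primary and secondary analyses are untouched; the weakness lies in the safety statement.

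A reader might infer that correcting this would let the trial show whether falls differ by arm, or exclude a risk above about 11%. Neither is supported. The 10.9% limit needs systematic data on all 26 per arm, and half the sample has already finished. With about 13 per arm the zero-event limit is 20.6%, or 17.1% to 25.9% if 16 to 10 remain in the arm. This rests on the 26 completions reported in November 2025, no change in the target of 52, and prompt adoption. The gain is an evenly collected descriptive count. The change is worth making, and each further completed participant reduces what it can deliver.

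**What to change.** In the Data Monitoring section, replace the informal rule with a short standard record for every remaining participant in both arms:

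1. Session staff complete a brief event log at every intervention session, including when nothing occurred.
2. At T2 and T3, add the same fixed questions to LimeSurvey for both arms: any fall, injury or new pain since the last contact. Place them after the balance-confidence scale and the performance tests, so that they cannot influence the primary outcome.
3. Someone other than the blinded assessor records circumstances and any relation to a session. A description of stumbling while practising with the aid would reveal the arm to the person scoring the WAST, Timed Up and Go and 6-Minute Walk Test.
4. Report counts by arm with exact intervals and no hypothesis test. Show session events separately from events reported at T2 and T3, because the session activities differ by arm.
5. Report events in participants who have already completed separately, labelled as informally captured.

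Cost: a few questionnaire items, a short log, brief instruction of session staff, time from an unblinded staff member when an event is reported, and a minor ethics amendment. No extra visit is needed. The limitation to state is that structured data will cover only about half the trial.
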